##### Cardiovascular monitoring

We will ask patients wear up to 2 wireless monitors at two different time points over the course of the study. Both activities are described below.

##### Zephyr BioPatch testing

The Zephyr BioPatch™ is a wireless monitor that can measure changes in heart rate and breathing rate, activity level and position, and Electrocardiogram (EKG) patterns. The BioPatch™ consists of a sensor, known as the BioModule™, which is less than 2 in. in diameter and weighs less than an ounce, and a lightweight plastic patch that holds the BioModuleTM in place. Comfortable and small, the BioPatch™ attaches to traditional disposable EKG electrodes placed on the chest and allows the BioModule™ to be easily snapped in. It is powered by a rechargeable battery. Patients will be asked to wear the BioPatch™ for a total of 48 h during which it will log their activity and heart rate data. At the end of 24 h, patients will need to recharge the sensor for a period of 3 h and then place it back on the chest for an additional 24 h. In addition, during the time they are wearing the device, they will be asked to keep a journal of their sleep and wake times, periods of exercise and any other events that might significantly affect biosensor readings. At the end of this period, they will be asked to return the BioPatch™ and journal. We will provide patients with a pre-paid envelope to return the device at their clinic visit.

##### ZIO® XT patch testing

The ZIO® XT patch is a small, adhesive, water resistant single lead EKG sensor that is placed on the chest to monitor heart rhythm. Patients will be asked to wear the ZIO® XT patch for a total of 14 days during which it will log their EKG patterns. At the end of the 14-day period, they will be asked to remove and return the ZIO® XT patch to iRhythm technologies in the prepaid envelope that will be provided to them at their clinic visit.

### Data and specimen banking

We will store blood and urine samples at a central laboratory at the University of Pennsylvania and at the NIDDK storage facility for future studies of kidney disease, heart disease, and their consequences. They will be connected to study results only by a unique study number, which will be assigned to each participant at the time of consent. The archived blood and urine samples can be used at any time during the period for more studies of kidney and heart disease. It is possible that new tests will be available in the future, which could be useful in understanding kidney and heart disease. Researchers who plan to use archived sample for future scientific study will be required to request and receive all of the necessary approvals or waivers from the NIDDK and CRIC study investigators before using the samples. Samples will only be released to scientists who are qualified and prepared to conduct a research study.

### Data analysis

#### Analytical plan for first aim

##### Overview of methods for statistical analysis

We plan to use standard descriptive statistics to characterize the overall study population and subgroups of interest both at baseline and during follow-up. Summary statistics such as means, medians, standard deviations, and ranges will be produced for measured variables. Frequencies will be tabulated for categorical and ordinal variables. Graphical methods will be used to examine distributions, identify potential influential points, and guide in data transformations. For outcomes collected longitudinally, and to examine associations among various measures, scatterplots and grouped boxplots will be produced to examine assumptions of linearity, symmetry, and homoscedasticity. For outcome-related analyses, we consider two primary types of analyses - failure-time analyses and repeated measures analyses.

##### Sample size and power considerations for first aim

We can calculate power for each of the analysis types for this aim. For brevity, we focus on the analyses that will have the least power to detect differences in outcomes (i.e., other analyses will be able to detect smaller differences). The analyses that will have the lowest power relative to the total sample size are those focusing on failure-time (e.g., CVD and ESRD) effects. For these analyses, power depends on: [1] outcome of interest [2]; baseline progression rate [3]; risk factor distribution [4]; significance level [5]; sample size; and [6] clinically meaningful effect size. Although we expect that there may be a number of factors associated with very large risk differences, we consider two-fold relative differences in risk to be clinically meaningful. Our proposed center will recruit 500 diabetic AI, and our primary analyses will be based on matched comparisons to participants of specific racial/ethnic backgrounds from the entire CRIC cohort. As we compare failure-time outcomes between AIs (*n* = 500) and another racial/ethnic group, we will have 80% power to detect HRs of at least 2.0 as long as we have an average of at least 3 years of follow-up within each group, and the lower-risk group has an annual event rate of at least 0.02 per year. The event rates for CKD progression observed in CRIC are higher than this: we expect greater than 95% power to detect HRs of at least 2.0, and 80% power to detect HRs of at least 1.67. Our power to detect a significant impact of an exposure on the HR comparing the AIs to another group will be lower. Still, if the AI HR is 2.0, with the current non-AI CRIC event rate in the non-AI group, then we will have 80% power to detect a significant impact of an exposure on the HR if the exposure reduces the HR by half – the pre-determined clinically meaningful effect. Therefore, we will have at least 80% power to detect clinically meaningful differences in CKD and CVD progression between AIs and other racial/ethnic groups.

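### Read as an effect on the between-group HR, the 80% power for an exposure that halves the AI HR does not agree with the same paragraph's 80% power at HR 1.67; about 42–49% is supported at 1:1 matching

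*Protocol article*

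**What the plan says.** All the figures are in the protocol article, section 'Sample size and power considerations for first aim'.

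- Size: "Our proposed center will recruit 500 diabetic AI".
- Comparator: the article says that "our primary analyses will be based on matched comparisons to participants of specific racial/ethnic backgrounds from the entire CRIC cohort". No matching ratio is given.
- Floor condition for 80% power at HR 2.0, follow-up: "an average of at least 3 years of follow-up within each group".
- Floor condition for the same statement, event rate: "the lower-risk group has an annual event rate of at least 0.02 per year".
- At the higher CKD-progression rates seen in CRIC: "we expect greater than 95% power to detect HRs of at least 2.0, and 80% power to detect HRs of at least 1.67". The rate itself is not given.
- Exposure question: the paragraph says power will be lower for an exposure's impact on the HR comparing AIs with another group. For an AI HR of 2.0 at the current CRIC rate in non-AIs it still claims "80% power to detect a significant impact of an exposure on the HR if the exposure reduces the HR by half".
- Closing sentence, on AIs against the other groups: "Therefore, we will have at least 80% power to detect clinically meaningful differences in CKD and CVD progression".

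**The concern.** An exposure that changes the AI-versus-other HR is an interaction on the log-hazard scale. The test compares the HR among the exposed with the HR among the unexposed, so its variance collects a term from each of four cells. With an even split its standard error is about twice that of the main effect. A study that can just detect a main-effect HR of 1.67 can then just detect a ratio of HRs of about 1.67² = 2.8, not 2.0. The paragraph claims 80% for 2.0.

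This is the only power statement for the exposure part of the first aim, and the article's study overview makes exposures one of its two overall goals. If true power is near one half, a non-significant interaction is quite likely even when an exposure does halve the HR. A reader who trusts the 80% would take that null result as evidence that exposure does not explain the AI excess.

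**Working it through.** **Inputs.** From the article: 500 AIs, 3 years' average follow-up, 80% power at HR 1.67, AI HR 2.0, ratio of HRs 0.5. Assumed: two-sided 0.05 (stated only for the second aim), 1:1 matching (varied to 5:1), and the same exposure prevalence in both groups (varied from 5% to 95%). Events in a cell = n(1 − exp(−rate × 3)). The squared sum of normal quantiles is (1.960 + 0.842)² = 7.849.

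**Step 1: the main-effect figures.**
- HR 2.0 at 0.02 per year, 500 v 500: 29.1 + 56.5 = 85.7 events. Schoenfeld power = Φ(0.693 × √(85.7/4) − 1.96) = 89%. The stated 80% is a conservative floor.
- HR 1.67 at 80%: 4 × 7.849 / (ln 1.67)² = 119.4 events. This gives a non-AI rate of about 0.032 per year (45.6 + 73.8 events).
- HR 2.0 at that rate: 45.6 + 87.0 = 132.6 events and 98% power, which agrees with the stated figure above 95%.

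So the main-effect statements are coherent with each other.

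**Step 2: a check that needs no event rate.** Main-effect SE = ln(1.67)/2.80 = 0.183. Doubled for an even split it is 0.366. Power for a halving = Φ(0.693/0.366 − 1.96) = 47%.

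**Step 3: four cells at 0.032 per year, 1:1, 50% exposed, exposure neutral in non-AIs.** Power = Φ(0.693/SE − 1.96), where SE² is the sum of 1/events over the cells.

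| Case | Non-AI unexposed, exposed | AI unexposed, exposed | SE | Power |
|---|---|---|---|---|
| HR 2.0 unexposed, 1.0 exposed | 22.8, 22.8 | 43.5, 22.8 | 0.393 | 42% |
| Overall AI HR 2.0 | 22.8, 22.8 | 56.3, 29.9 | 0.373 | 46% |

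The best prevalence (53–55%) adds less than one point. Calibrating the rate with a Wald variance (0.034 per year) and averaging the HR on the log scale gives the top of the range, 49%. In the overall-HR-2.0 case, power falls to 37% at 30% exposed and 28% at 20%. For comparison, 80% power needs at least 16 × 7.849 / (ln 2)² = 261 events even with equal cells, about twice the 132.6 available.

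**Step 4: more comparators, recalibrated each time to 80% at HR 1.67.** With overall AI HR 2.0 and 50% exposed: 53% at 2:1, 57% at 3:1, 61% at 5:1. At 5:1 and the best prevalence (61%), the cells are about 63.2, 98.8, 34.2 and 28.0. SE is 0.301 and power 63%. Averaging the HR on the log scale instead makes the AI cells 36.1 and 29.6, SE 0.296 and power 65%. Under Wald calibration the 5:1 figures are lower, down to 42%.

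**Step 5: what 80% would require at 1:1.** A non-AI rate of about 0.077–0.088 per year. The detectable main-effect HR there is 1.43–1.41, not 1.67.

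**Step 6: the contrast that comes near 80%.** Exposed versus unexposed AIs, HR 2.0 to 1.0, at 0.032 per year. Power = Φ(0.693 × √(p(1 − p)d) − 1.96), with p the exposed share and d the AI events.

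| Exposed | AI events | Power |
|---|---|---|
| 50% | 43.5 + 22.8 = 66.3 | 81% |
| 30% | 60.9 + 13.7 = 74.6 | 78% |
| 20% | 69.6 + 9.1 = 78.7 | 69% |

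A Wald calculation at 50% gives 76%. If the overall AI HR is 2.0 instead, Schoenfeld power is 90%, 84% and 73%.

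**The case against.** **The paragraph names no interaction test.** This is the strongest defence. The study overview speaks of exposures peculiar to AIs in the Southwest. If no comparator is exposed, there are no four cells, and the effect on the AI-versus-other HR reduces to exposed versus unexposed AIs. Step 6 then returns 81% at 50% exposed, almost exactly the stated figure. The Discussion also asks whether exposures partly account for the group differences. That could mean attenuation of the AI HR on adjustment, which is again not an interaction. This stands as far as it shows that the 80% is not impossible under every reading. It does not rescue the sentence. The within-AI contrast takes nothing from the comparator group, while the sentence is about the HR between groups. It also holds only at a prevalence near one third to one half, which the article does not state.

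**The inputs are back-solved.** True: matching ratio, prevalence, CRIC rate and the first aim's alpha are not given. An article may leave these to the full protocol, so their absence is not the complaint. The complaint is that two stated figures do not fit together, and step 2 shows this without the rate. The back-solve does treat 80% at HR 1.67 as exact, although the paragraph's other 80% figure is conservative.

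**Stronger readings that the documents do not support.**
- A reader might take 46% as a ceiling. It is one case: 1:1, 50% exposed, overall AI HR 2.0. Other calibrations and larger comparators go higher.
- A reader might expect more power if the exposure also doubles risk in non-AIs. That holds only if the average non-AI rate is allowed to rise above the CRIC rate. Held at 0.032, with 50% exposed and overall AI HR 2.0, the cells are 15.4, 29.9, 43.5 and 43.5, SE 0.380 and power 45%.
- A reader might infer that the closing sentence is false. It concerns differences between groups, and the main-effect figures support it.

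**Conclusion.** The point holds for the sentence as written. Taken as a test of whether exposure changes the between-group HR, the 80% does not agree with 80% power at HR 1.67. The supported power is about 42–49% at 1:1 and the most favourable prevalence, lower at 20–30% exposed, and about 63% with five comparators per AI (65% with log-scale averaging). No case run at the calibrated rate reaches 80%.

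This rests on the interaction reading, two-sided 0.05, equal prevalence in both groups, and taking the 1.67 figure at face value. It does not show a contradiction under every reading: the within-AI contrast gives about 80% at 30–50% exposed, but that is another question. The main-effect power statements are sound and unaffected.

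**What to change.** Do one of two things in the first-aim power paragraph.

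1. Keep the between-group question and restate its power as roughly 42–49% at 1:1, or up to about 63% with a larger comparator. Give the exposure prevalence in each group, the comparator size and the event rate behind the figure.
2. Define the powered exposure question as exposed versus unexposed within AIs at a stated prevalence (about 81% at 50% exposed, 78% at 30%, 69% at 20%, for HR 2.0 to 1.0). Label the AI-by-exposure interaction exploratory.

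In both cases, name the test. The closing sentence can stay if it is confined to the main-effect comparison of groups. The cost is the wording of one paragraph and one less favourable figure; design, sample size and data collection do not change.

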##### Recruitment site (center) effects

There may be systematic differences among participating sites (urban vs reservation base) in subject mix and methods of treatment. However, only some of these differences are likely well-characterized. Therefore, we will need to account for potential center/cluster effects to get appropriate estimates of standard errors, and possibly to control for confounding by center. We will consider several ways to account for center in survival models; by fitting mixed- or fixed-effects models including separate center-specific coefficients, by fitting marginal models, and by using models that stratify on center. For prediction in a wider population, the centers will not themselves be of interest; thus, we will rely primarily on marginal models using the robust variance estimator.

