**Method:**

We will establish 3 clinical centers to recruit AIs from the Southwest United States (US) to expand the Chronic Renal Insufficiency Cohort (CRIC) study. We will follow the current CRIC protocol for kidney and cardiovascular measures and outcomes, which include ambulatory monitoring of kidney function and the use of mobile health technologies for CVD sub-phenotyping, and compare the outcomes in AIs with those in other racial/ethnic groups in CRIC.

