## Methods/design

### Study overview

The overall goals of the proposed prospective cohort study are to: (a) precisely assess the extent to which the rates of CKD and CVD progression differ between AIs and other racial/ethnic groups based on standardized definitions used throughout CRIC; and, (b) to identify the association of CKD to the levels of potential environmental and occupational exposures unique to AIs residing in the American Southwest. To better understand the natural history of CKD/CVD in this high-risk population, we will implement the CRIC 2018 protocol of ambulatory monitoring of kidney function and damage along with evaluations of CVD sub-phenotypes using mobile health technologies. Data collection will take place at three sites located across the Southwest US. We will adopt the general methods and procedures of the parent CRIC protocol (http://www.cristudy.org).

We obtained Letters of Support from Zuni Comprehensive Community Health Center - Indian Health Services, First Nations Community Health Source, Pueblo of Zuni Tribal Governor, and NIDDK, NIH Phoenix.

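### Centre effects are to be handled mainly by a robust variance, but with only three American Indian (AI) centres an uncorrected centre-clustered variance is too small

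*Protocol article*

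**What the plan says.** The article's section on recruitment site (center) effects expects systematic differences between sites, such as urban against reservation-based, only some of them well characterised. It concludes: "Therefore, we will need to account for potential center/cluster effects to get appropriate estimates of standard errors". It also mentions possible control of confounding by centre.

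It then lists the ways to be considered in survival models: "by fitting mixed- or fixed-effects models including separate center-specific coefficients, by fitting marginal models, and by using models that stratify on center". Because centres are not of interest when results are carried over to a broader population, it makes a choice: "thus, we will rely primarily on marginal models using the robust variance estimator".

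The number of AI centres is fixed in the Study overview: "Data collection will take place at three sites located across the Southwest US". The Abstract also gives three. The comparison is set in the sample size section for the first aim: "our primary analyses will be based on matched comparisons to participants of specific racial/ethnic backgrounds from the entire CRIC cohort". The first aim covers both risk factors among AIs and the comparison of event rates with other CRIC groups.

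**The concern.** A cluster-robust variance is estimated from the spread of cluster totals, so its reliability depends on the number of clusters and not on the number of participants. A risk-factor analysis within AIs has three clusters in all. In AI versus other, the whole AI contribution to the variance comes from three. The estimate is then biased downward and very noisy, and comparing the statistic with a normal distribution makes matters worse. This happens even if the centres do not truly differ.

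At stake is the first aim. Intervals for exposures tested within AIs, and for AI-versus-other hazard ratios, would be too short, and the risk of false-positive findings would be raised. A second difficulty is structural. The AI centres recruit AIs and the comparators come from the parent cohort, so centre and AI status cannot be told apart in that contrast.

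**Working it through.** **Inputs from the article.** Three AI centres; 500 AIs; average follow-up of 3 years; HR 2.0; 0.02 events per year in the lower-risk group.

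**Assumptions.** 500 comparators; 7, 10 or 13 comparator centres; between-centre log-hazard SD 0 to 0.3; two-sided 5% (stated only for the second aim); equal-sized centres; no matching; variance clustered on centre with no small-sample correction.

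**1. The plan's own power figure.** HR 2.0 at 80% needs 4(1.96 + 0.8416)²/(ln 2)² = 65.3, so 66 events. Expected events are 500(1 − e^−0.06) + 500(1 − e^−0.12) = 29.1 + 56.5 = 85.7. Power is Φ(√(85.7/4) × 0.693 − 1.96) = 89%. Using 1/d_AI + 1/d_other as the variance gives about 86%. The stated 80% is therefore below the recomputed figure. Attrition of roughly 20–25% (82–79%) or a design effect of 1.30 would close the gap.

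**2. Within AIs, by hand.** With K equal clusters, the uncorrected robust variance is distributed as V·χ²(K−1)/K, where V is the true variance. The z statistic is then √(K/(K−1)) times a t variable on K−1 degrees of freedom. For K = 3, rejecting at |z| > 1.96 means |t₂| > 1.96 × √(2/3) = 1.600. For two degrees of freedom, P(|t₂| > c) = 1 − c/√(2 + c²) = 1 − 1.600/√4.561 = **25.1%**.

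**3. Within AIs, by simulation** (Poisson approximation to the Cox model, rate 0.06, exposure in 50% of participants, unrelated to centre):

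| Method | Type I error, SD 0–0.3 |
|---|---|
| Centre-clustered robust variance | 25–26% |
| Ordinary individual-level variance | 4.6–4.9% |
| Stratified by the three centres | about 5% |

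**4. AI versus other, by hand.** If each side contributes half the variance, the expected robust SE is √[(2/3 + (K−1)/K)/2] of the true SD: 0.87 with 7 comparator centres and 0.89 with 13. The simulated ratios at SD 0 are 0.87 and 0.88.

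**5. AI versus other, by simulation** (type I error under HR 1):

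| Rate per year | SD | Clustered robust | Individual-level |
|---|---|---|---|
| 0.02 | 0 | 11–13% | about 5% |
| 0.02 | 0.2 | 12–14% | about 8% |
| 0.02 | 0.3 | 13–14% | 11–13% |
| 0.03 | 0 | 11–13% | about 5% |
| 0.03 | 0.2 | 12.5–14% | 9–10% |
| 0.03 | 0.3 | 14–15% | 15–17% |

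The ranges run over 7 to 13 comparator centres. A direct Cox fit with 3 versus 7 centres, SD 0.2 and rate 0.02 gave a robust SE of 0.252 against a true SD of 0.302, and 84.9% coverage of nominal 95% intervals. Coverage comes close to nominal only with many centres: 93.9% with 20 per side and 94.7% with 40.

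**6. What a correction does.** A K/(K−1) factor with t on 2 degrees of freedom gives 98.7–99.8% coverage. With 7 comparator centres it leaves 22%, 14% and 9% power for HR 2.0 at SD 0, 0.2 and 0.3.

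**7. Aliasing.** With 3 AI and 7 other centres, the ten centre indicators have rank 10. Adding the AI indicator leaves rank 10 with 11 columns. The centre-stratified Cox information for AI status is exactly 0.

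**The case against.** - **The clustering unit is not named, and a correction may sit in an analysis plan that is not shown.** Both are true. However, the section turns to the robust variance in order to get standard errors right for centre, and it serves that purpose only if clustered on centre. A correction would protect the error rate, but the one tried removes most of the power, and none separates AI status from AI centre.

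- **Individual-level variance is not a clean replacement for AI versus other.** This stands. It holds 5% only when centres do not differ. At SD 0.3 it is little better than the robust estimator (rate 0.02) or slightly worse (rate 0.03). Calling the result conditional on the participating centres changes the question, and the article wants results that extend more widely. The difficulty is a limit of a three-centre design.

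- **A reader might infer that two of the listed methods fail for the primary hazard ratio.** The algebra is right if parent-CRIC centres contribute no AI participants, which the article implies but does not state. But the article offers a general list and never assigns fixed-centre or stratified models to that contrast. Both work for risk factors within AIs. This calls for a clarification only.

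- **A reader might infer that the first-aim power ignores centre variation.** The article does not support this. It gives no method, its 80% lies below the recomputed 86–89%, and the Discussion indicates that some dropout was allowed for. What fills the gap is unknown.

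**Conclusion.** The concern holds in a limited form. The stated primary method, read as clustered on centre and used without correction, gives standard errors that are too small with three AI centres.

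Within AIs the type I error is about 25%. This needs no assumption about comparator centres and hardly depends on the between-centre SD. For AI versus other it is about 11–15%, subject to the assumed 7–13 comparator centres, SD 0–0.3 and 500 unmatched comparators.

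A specific remedy exists within AIs. For AI versus other the plan can avoid the worst method and state the limitation, but reanalysis cannot remove it. No error in the power statement is established.

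**What to change.** 1. **Risk factors within AIs.** Make a Cox model stratified by the three centres, with ordinary individual-level variance, primary in place of the centre-clustered robust variance. Cost: inference applies to these three centres, and an exposure that differs mainly between sites is informed only by its within-centre contrast.
2. **AI versus other.** Say that fixed-centre and centre-stratified models do not apply, because AI status is constant within the AI centres. Do not rely on an uncorrected centre-clustered variance. State that the AI effect cannot be separated from AI-centre effects, and that individual- or pair-level intervals leave out between-centre variation. Add a random-centre model and leave-one-AI-centre-out analyses as sensitivity analyses. Cost: a few extra analyses and a more guarded claim about a wider population.
3. **Power statement.** At most, add a sentence saying whether between-centre variation is included.

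Recruitment, visits and measurements are unaffected.
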